**Fig. 1 Fig1:**
[figure not shown]
Time schedule of enrolment. T0: 1–3 weeks pre-surgery, T1: postoperative week*, T2: 2 months follow-up, T3: 6 months follow-up, T4: 12 months follow-up. e-CBT, online cognitive behavioral therapy; EDU, online educational therapy; TAU, treatment as usual; QST, quantitative sensory testing; CPM, conditioned pain modulation

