### Inclusion criteria for the RCT (e-CBT&EDU)

Women scoring either ≥ 8 on the anxiety subscale of the Hospital Anxiety and Depression Scale (HADSa) [52], ≥ 3 on the Surgical fear item (i.e., “quite a bit” or “very much” [16];), ≥ 5 on the Concerns about Recurrence Scale (CARS) [53], or ≥ 18 on the Pain Catastrophizing Scale (PCS) [54]

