**Day of surgery**	
**Session 2: **DoS + 7 days - Education: relationship between thoughts-feelings-bodily sensations-behavior; coping with anxiety; valued activities - Exercises: thoughts and activity diary	
**2nd appointment with the therapist:** introduction relaxation exercises and thoughts diary; discussion potentially hindering factors	
**Session 3: **DoS + 14 days - Education: different coping strategies; unhelpful and helpful thoughts - Exercises: cognitive restructuring	
**Session 4: **DoS + 21 days - Education: role of avoidance - Exercises: clarifying valued activities; SMART description of new valued activities	
**Session 5: **DoS + 28 days - Recap session 1-4 - Action plan: warning signs and helpful exercises and techniques	
**3rd appointment with the therapist:** discussion on helping thoughts, valuable activities, action plan; evaluation of most helpful elements of the program and how to continue	

*DoS* day of surgery, *SMART* Specific-Meaningful-Acceptable-Realistic-Time framed

Session 1 starts with discussing the reactions that can be expected when confronted with breast cancer and the upcoming surgery. The education part is devoted to pain, the different factors contributing to the pain experience, and the stress response. Relaxation techniques are introduced. Patients are asked to try out the different relaxation exercises (progressive muscle relaxation, breathing exercises and visualization exercise). As a recurring aspect of the intervention, patients choose one exercise and continue to practice this exercise on a daily basis.

Session 2 consists of three parts, the first being the relation between thoughts-feelings-bodily sensations-behavior. With the aid of a thoughts diary, patients learn to notice their own thoughts and reactions. Later in the intervention, this will serve to practice cognitive restructuring of the catastrophizing thoughts. The second part focuses on coping with anxiety and contains tips and exercises. The last part of the session concentrates on finding a good activity-rest balance after the surgery. Patients are encouraged to engage in pleasant or valued activities. After session 2, patients are asked to continue the relaxation exercises, write down their thoughts about cancer, pain, and other complaints in the thoughts diary, and document their pleasant and valued activities.

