#### Secondary study parameters/endpoints

Secondary outcomes of the study are pain intensity scores (intercept and slope) during the first postoperative week (NRS, pain diary), cessation of postoperative opioid use (no. of days), and PPBCT prevalence after 12 months. Mean PPBCT intensity in the operated area (NRS), presence of neuropathic pain (Doleur neuropathique (DN4)) [59], and pain interference (Brief Pain Inventory (BPI) [60], measured at 2, 6, and 12 months.

(Pain) sensitivity is assessed with quantitative sensory testing (QST) before and at 6 months post-surgery. QST is measured at the bilateral pre-axillary dermatomes Th 3. In patients with persistent postoperative pain in the operated area, the 6-month QST measurement is performed in the painful and the corresponding contralateral location. QST measurements are performed according to the protocol developed by the DFNS [61]. Conditioned pain modulation (CPM) is measured before, at 1 week postoperatively and 6 months later according to the suggestions of Yarnitsky et al. [62]. The chosen CPM algorithm compares three repetitions of pressure pain threshold measurements in the thenar contralateral to the operated side, before and immediately after a cold pressor test delivered to the other hand with ice water.

In addition the psychological parameters anxiety, fear of recurrence, catastrophizing, and depression are assessed together with the cancer related quality of life before and up until 12 months after surgery.

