#### Secondary study parameter(s)

The mean daily postoperative pain scores over the 1-week period will be compared between the groups using linear mixed-effects regression with a random intercept and slope to account for multiple measurements over time within patients. Covariance between random effects will be estimated using an unstructured covariance matrix. Correlation between measurements over time will be modeled using a first order autoregressive structure. Both differences in average pain level over time and differences in trend across time will be assessed.

Time to opioid cessation will be analyzed with the Kaplan-Meier method and compared using the log-rank test.

Mean pain intensity and pain interference at 2, 6, and 12 months will be compared using linear mixed-effects regression with regards to group differences and time course.

Quality of life at 6 and 12 months will be compared between groups using the independent-samples *t*-test.

The effect of surgery on QST and CPM parameters will be analyzed by paired-sample *t*-test on the pre-surgical and 1-week and 6-months post-surgical results. The intervention effect on QST and CPM will be assessed with linear mixed-effects regression at the three time points.

Intervention effects on pain catastrophizing, anxiety, depression and fear of cancer recurrence at two months will be evaluated using the independent-samples *t*-test. With linear mixed-effects, regression differences in level and slope are compared between e-CBT and EDU taking all longitudinal measurements into account.

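### For the four psychological outcomes, the level-and-slope comparison appears to count the pre-randomization score as an outcome visit and fits a straight line over 0 to 12 months; adjusting for T0 and reporting each visit costs almost nothing

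*Protocol article*

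**What the plan says.** All references are to the protocol article.

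- **Psychological outcomes, 2 months.** Secondary study parameter(s), under Statistical methods: "Intervention effects on pain catastrophizing, anxiety, depression and fear of cancer recurrence at two months will be evaluated using the independent-samples" t-test.
- **Psychological outcomes, longitudinal.** The next sentence adds a mixed model in which "regression differences in level and slope are compared between e-CBT and EDU taking all longitudinal measurements into account".
- **When they are measured.** The Outcomes section has these variables "assessed together with the cancer related quality of life before and up until 12 months after surgery". Table 2 marks PCS, HADS-A, PROMIS depression and CARS at T0, T2, T3 and T4. Fig. 1 gives the follow-up times: "T2: 2 months follow-up, T3: 6 months follow-up, T4: 12 months follow-up".
- **T0 precedes allocation.** Entry to the RCT depends on scores such as "≥ 8 on the anxiety subscale of the Hospital Anxiety and Depression Scale (HADSa"), with similar cut-offs on CARS and PCS. Depression is not an entry criterion but is listed at the same T0 assessment.
- **Pain intensity and interference.** "Mean pain intensity and pain interference at 2, 6, and 12 months will be compared using linear mixed-effects regression". No T0 outcome is listed here, although Table 2 marks NRS and BPI at T0.
- **QST and CPM.** "The intervention effect on QST and CPM will be assessed with linear mixed-effects regression at the three time points". Table 2 marks CPM at T0, T1 and T3, and QST at T0 and T3 only.
- **Timing of the intervention.** Table 1 recommends the last session 28 days after surgery.

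**The concern.** Randomization makes the expected arm difference at T0 zero. A contrast that averages T0 together with the follow-up visits therefore pulls the estimate toward zero. A linear slope over 0 to 12 months suits an effect that builds steadily. The last session is recommended about a month after surgery and the protocol itself tests for an effect at 2 months, so an effect already present at 2 months, which then holds or fades, is at least as likely. A straight line fits that shape badly.

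At stake is what the trial can say about the psychological outcomes over the year. Objectives {7} makes their course up to 12 months a secondary objective, and the mixed model is the only planned analysis of these outcomes that reaches 6 and 12 months.

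**Working it through.** **The plan's own figure.** The article gives no figure for these mixed models. The arm size comes from Sample size {14}, which reproduces: (1.960 + 0.842)² × (0.50×0.50 + 0.25×0.75) / 0.25² = 54.94, so 55 per group; 55/0.8 = 68.75, so 69 per group and 138 in total. I use n = 55 per arm with complete data.

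**Assumptions not in the article.** Standardized effect d = 0.5 SD; equal correlation ρ = 0.5 between any two visits (range 0.3 to 0.7); true arm difference 0 at T0 and d at 2, 6 and 12 months; two-sided alpha 0.05; normal approximation, power = Φ(z − 1.96).

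**Estimates.**
- Average level over four visits: (0 + d + d + d)/4 = 0.75d.
- Straight line through (0, d, d, d) at t = 0, 2, 6, 12 (mean 5, sum of squares 84): slope = 5d/84 = 0.0595d per month; intercept = 0.75d − 5 × 0.0595d = 0.452d.
- Fitted differences: 0.45d at T0 (true 0), 0.57d at 2 months, 0.81d at 6 and 1.17d at 12 (true d at each).
- If level means the group coefficient at month 0 in a model with an interaction, it estimates 0.45d, not 0.75d.

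**Power at d = 0.5, ρ = 0.5 (variances in SD²).**

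| Analysis | Effect | Variance | z | Power | Power, ρ 0.3 to 0.7 |
|---|---|---|---|---|---|
| Level, 4 visits | 0.75d | (2/n)(1+3ρ)/4 | 2.487 | 0.701 | 0.61 to 0.81 |
| Linear slope | 5d/84 | (2/n)(1−ρ)/84 | 2.023 | 0.525 | 0.40 to 0.74 |
| Follow-up mean, unadjusted | d | (2/n)(1+2ρ)/3 | 3.211 | 0.895 | 0.83 to 0.95 |
| Follow-up mean, T0 as covariate | d | (2/n)[(1+2ρ)/3 − ρ²] | 4.062 | 0.982 | 0.98 to >0.99 |
| 2-month t-test as planned | d | 2/n | 2.622 | 0.746 | 0.746 |
| 2 months, T0 as covariate | d | (2/n)(1−ρ²) | 3.028 | 0.857 | 0.79 to 0.96 |

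Level and slope are orthogonal contrasts here, so a joint 2-df test has noncentrality 2.487² + 2.023² = 10.28 and power 0.827.

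**Other effect shapes.**
- Fading (d, 0.75d, 0.5d): level (0 + 1 + 0.75 + 0.5)/4 = 0.56d, against a follow-up mean of 0.75d; again a quarter is lost. The fitted slope is +0.015d per month, so the line shows a growing effect while the true one halves.
- Growing (d/3, 2d/3, d): the line fits better, 0.10d at T0 and 1.06d at 12 months, and the slope has power 0.77.

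**QST and CPM.** If the mixed model averages over all visits, CPM gives (0 + 1 + 1)/3 = 0.67 of an effect present from week 1, a third lost, and QST gives (0 + 1)/2 = 0.50, half lost. QST has two time points in Table 2, so three is wrong for it whatever the model.

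**Models not affected.** Pain intensity and interference at 2, 6 and 12 months: (1 + 1 + 1)/3 = 1.00, no dilution. The diary model uses postoperative days only.

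**The case against.** **The article does not say outright that T0 is an outcome or that time is linear.** Both are inferred, and a fuller protocol or SAP may settle them. That stands as a caution. But the inference is strong: the sentence takes in all longitudinal measurements, Table 2 includes T0, slope most naturally means a linear trend, no baseline adjustment is named, and the pain model two paragraphs earlier restricts itself to follow-up visits.

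**An undiluted test is already planned.** The 2-month t-test examines the same four outcomes. This stands, and it limits the harm. It does not use T0, and it leaves 6 and 12 months uncovered.

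**Separate power figures make the plan look weaker than it is.** Level and slope are both examined; jointly they reach about 0.83. Part of the 0.98 is efficiency from the covariate; leaving T0 out of the outcomes without adjusting already gives 0.895. Both points stand.

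**The step-shaped effect is an assumption.** Patients go at their own pace and the last session is about continued practice, so a growing effect is plausible, and then the slope performs well. This stands too; it is why the figures are illustrations only.

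**Stronger readings.** A reader might infer that all the mixed models are diluted by a quarter. The diary and pain intensity/interference models do not list T0 as an outcome, and the fraction for QST/CPM differs. A reader might also infer that a real effect on anxiety or catastrophizing would be missed. The 2-month t-test and the joint power do not support that.

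**Conclusion.** The point holds for the longitudinal comparison of pain catastrophizing, anxiety, depression and fear of recurrence. On the natural reading, the average-level contrast loses a quarter of an effect that is constant from 2 months on, and a linear slope misdescribes an effect that appears by then. The quarter follows from the visit schedule; the power figures rest on the assumed effect size, correlation and shape. The QST/CPM sentence has the same weakness to a different degree if it averages over visits, and its count of time points needs correcting for QST in any case. The primary analysis and the sample size are untouched. This is a free improvement to secondary analyses, not a threat to the trial's main conclusion.

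**What to change.** - **Four psychological outcomes.** Model 2, 6 and 12 months as categorical outcome visits with a group-by-visit term and the T0 score as covariate (or keep T0 in the model with a common baseline mean for both arms). Report the adjusted arm difference at each visit and averaged over follow-up, in place of the linear level-and-slope comparison.
- **2-month comparison.** Take it from the same model, so that it too is adjusted for T0.
- **CPM.** Analyse 1 week and 6 months, adjusted for T0.
- **QST.** Analyse 6 months by ANCOVA on T0, and correct the number of time points.
- **Leave as they are.** The diary model and the pain intensity/interference model need no change on this account.

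Cost: a change of wording before the analysis and a few more fixed-effect parameters. A linear model with interaction has four (intercept, group, time, group-by-time); the categorical model has seven (three visit means, three arm differences, one baseline coefficient). No new data are needed, since T0 is already collected.

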#### Other study parameters

Other parameters including clinical and psycho-social patient characteristics, breast-cancer treatment related variables, and compliance with the psychological intervention are assessed at the time points shown in Table 2.

#### Interim analyses {21b}

After randomization of 50 patients, the effect size for the primary outcome will be computed to assess whether the assumptions made for the sample size calculation were correct. As the responsible statistician is not authorized to decide about the progress of the study—only to give advice about the sample size—the interim analyses will bear no effect on conclusions of effectiveness, but may be used to recompute the necessary sample size.

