#### Sample size {14}

The sample size calculation has been performed for the primary outcome, the prevalence of PPBCT (NRS ≥ 3) at 6 months after surgery for breast cancer. The expected overall prevalence of PPBCT is 30%, but the high anxiety/high catastrophizing group, which we will recruit for the randomized trial, has been shown to have a 2.2 times higher prevalence [15, 16, 69], and we expect that about 30% of all patients will screen positive for anxiety/catastrophizing [16, 55, 70]. To be on the conservative side for our calculation, and in accordance with Burns and Moric, we estimate that the prevalence of PPBCT will be 50% in the high anxiety/catastrophizing group [71] and also that perioperative CBT decreases PPBCT prevalence by 50%.

For the current study, this would mean a reduction of the prevalence in the e-CBT group from 50 to 25%. We need to include 55 patients per group to obtain 80% power to detect this difference, with an alpha of 0.05. To account for a potential drop-out rate of 20%, we will recruit a total of 138 high anxiety/catastrophizing patients. All patients that are considered to have low anxiety/catastrophizing and thus are not randomized will be asked to participate in the cohort study. We expect to include around 322 low anxiety/catastrophizing patients based on an expected 30/70% ratio of high vs low anxiety/catastrophizing.

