#### Composition of the data monitoring committee, its role and reporting structure {21a}

A DMC was not deemed necessary because the AMAZONE e-CBT and EDU intervention are low-risk interventions.

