## Trial status

The actual protocol version is V4-amendement-2/2022-02-21. Recruitment started in June 2021. To date, 130 patients have been recruited at six study sites in the Netherlands*. The first patient was included June 21, 2021. Planned termination of inclusion is June 2023.

*Study sites: Antoni van Leeuwenhoek Ziekenhuis – The Netherlands Cancer Institute, Amsterdam; Alexander Monro Breastcancer Hospital, Bilthoven; Reinier de Graaf Hospital, Delft; University Medical Center UMCG Groningen, Radboud University Medical Center, Nijmegen; Maastricht University Medical Center+ (MUMC+), Maastricht.

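### The interim look may reset the sample size from the observed between-arm effect, and the reason given for why this leaves the conclusions untouched does not protect the type I error

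*Protocol article*

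**What the plan says.** Protocol article, Interim analyses {21b}: once 50 patients have been randomized, "the effect size for the primary outcome will be computed to assess whether the assumptions made for the sample size calculation were correct". The statistician may advise on sample size but not decide on the progress of the trial. From this the section concludes that "the interim analyses will bear no effect on conclusions of effectiveness, but may be used to recompute the necessary sample size".

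Sample size {14} gives the assumptions to be checked: "a reduction of the prevalence in the e-CBT group from 50 to 25" percent, and "We need to include 55 patients per group to obtain 80% power to detect this difference, with an alpha of 0.05". With 20% drop-out this becomes 138 randomized.

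The primary endpoint is read six months after surgery (Outcomes {12}). The primary test is a logistic regression adjusted for the stratification variables (Statistical methods {20a}, primary study parameter), with no adjustment for the interim. The outcome analysis is done by an independent statistician blinded to the type of intervention (Who will be blinded {17a}). On oversight, "A DMC was not deemed necessary" (section {21a}).

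**The concern.** An effect size for the primary outcome is the e-CBT versus EDU contrast, so this is a comparative re-estimation. Hiding which arm is which does not turn it into a pooled one. When the observed contrast sets the final n and the same data then enter an unadjusted test, the test no longer holds its nominal level. Who takes the decision is irrelevant to that mechanism.

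Three things are at stake: the level of the primary test, whether a look at 50 patients can inform the planning assumptions at all, and when the look takes place. The trigger is a count of randomizations, while the quantity to be computed exists only six months after surgery.

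**Working it through.** **1. The plan's own figure.** Inputs from Sample size {14}: 50% versus 25%, power 80%, alpha 0.05 (taken as two-sided, which reproduces the stated n). Unpooled two-proportion formula:

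n = (1.96 + 0.8416)² × (0.50×0.50 + 0.25×0.75) / 0.25² = 7.849 × 0.4375 / 0.0625 = 54.9, so 55 per group.

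110 / 0.8 = 137.5, so 138. Both stated figures reproduce.

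**2. Type I error if n follows the interim effect.** The document gives no rule, so I assume n is reset to give 80% power at the observed effect, within limits, and the final test is unadjusted at 1.96. In the normal approximation, with n₁ per arm at the look and interim statistic z₁:

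N(z₁) = n₁ × (2.8016 / |z₁|)², cut to the allowed range

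P(reject | z₁) = 1 − Φ[(1.96√N − √n₁·z₁)/√(N − n₁)] + Φ[(−1.96√N − √n₁·z₁)/√(N − n₁)]

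Averaging over a standard normal z₁ with n₁ = 25:

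| Allowed n per arm | Two-sided error |
|---|---|
| 55 fixed | 5.0% |
| 55 to 110 | 5.9% |
| 55 to 220 | 6.5% |
| 25 to 110 | 6.9% |
| 25 to 220 | 7.5% |

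Binomial simulation with a pooled z-test, common prevalence 37.5% or 50% and 20-25 outcomes per arm gives about 5.8-6.7% when n may only rise and about 7-8% when it may also fall. The fixed design gives 4.5-5.2% in the same simulations.

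**3. Precision of the look with all 50 outcomes in hand.** If 50% versus 25% is exactly true, with 25 per arm:

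SE = √[(0.25 + 0.1875)/25] = √0.0175 = 0.132

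95% CI = 25 ± 1.96 × 13.2 = −0.9 to 50.9 points

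The half-width (25.9 points) is as large as the effect being checked. With 20 per arm the interval is −4.0 to 54.0 points. In simulation with 25 per arm, the recomputed n (not allowed below the 25 already in) has a median of 59. It exceeds 110 per arm in about 29% of trials and is 40 or less in 36%. Correct assumptions would often lead to advice to double the trial or to cut it sharply.

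**4. Timing.** Trial status: recruitment began in June 2021 and "Planned termination of inclusion is June 2023", about 24 months. Assuming even accrual of the 138:

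- Rate: 138/24 = 5.75 per month.
- 50th randomization: 50/5.75 = month 8.7.
- With a 6-month outcome then: (8.7 − 6) × 5.75 = about 15.5, or (8.7 − 6.5) × 5.75 = about 12.6 if surgery follows two weeks after randomization.
- If all 50 outcomes are awaited: month 14.7, with 14.7 × 5.75 = about 85 randomized.

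Steps 2 and 3 assume 20-25 outcomes per arm, which means waiting. They do not describe a look taken at the 50th randomization. At 6-8 outcomes per arm, upward-only re-estimation gives only 5.1-5.7% in simulation, and the effect estimate is then noisier still.

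**The case against.** **The sentence on conclusions can be read narrowly.** It may mean only that no efficacy or futility decision is taken at the interim, which is true. Recomputation is optional, no mechanical rule is stated and a reduction is not mentioned. This stands: the inflation is conditional, and the 7-8% range needs permission to cut n. It does not rescue the reasoning, because the section goes from an advisory role to no effect on conclusions while allowing n to follow the observed effect.

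**A condensed article may leave the rule, cap and any adjustment to the full protocol or SAP.** This also stands, and their absence is not the point here. The point is what the article states: a comparative look, and a safeguard that does not work.

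**The timing wording allows for waiting.** The look comes after 50 randomizations, not necessarily at that moment, and an effect on a 6-month outcome presupposes 6-month data. So it does not follow that the look is certainly too early, only that the text leaves the moment open. Early accrual may also have differed from the even rate assumed.

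**A reader might infer that, without a DMC, the running treatment effect reaches those who conduct the trial.** The document does not say so. It names an independent statistician, blinded to the type of intervention, whose stated output is advice on sample size. A changed n could hint at the effect, but no section passes the estimate on.

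**Conclusion.** The point holds in this form. The advisory role of the statistician does not protect the primary test. If the advice is followed and the final logistic regression is unadjusted, the two-sided error is about 5.8-6.7% with increases only and about 7-8% if reductions are allowed. This rests on a rule that resets n to 80% power at the observed effect, assumed caps of 2-4 times 55 per arm, and 20-25 outcomes per arm at the look. Some rules would hold the level, such as an increase only after a promising interim or a combination test, but the article states none.

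Separately, and whatever rule is used, 50 patients cannot confirm or refute 50% versus 25%. The trigger should be tied to completed outcomes so that the look has one defined moment.

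**What to change.** Trigger the look when 50 randomized patients have 6-month data, and choose one of the following:

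- **(a) Blinded review.** Estimate the 6-month prevalence with the arms combined and compare it with the planned (50 + 25)/2 = 37.5%. Recompute n for the fixed 50% relative reduction, upward only, with a stated cap. Do not compute the arm contrast.
- **(b) Effect-based look.** Keep it, but pre-specify the rule and the cap, and use a combination or conditional-error test for the final analysis.

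In either case, delete or correct the sentence that the interim has no effect on conclusions of effectiveness.

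The cost is mostly wording, but (a) has a real price. It checks the overall rate and not the assumed reduction: 50% versus 40% and 60% versus 30% both pool to 45%. A high pooled rate caused by a weak effect would not raise n. It is also imprecise: 1.96 × √(0.375 × 0.625/50) = ±13.4 points. Option (b) keeps the noisy estimate of the effect and adds complexity to the final test. Waiting for 6-month data means about 85 patients are already randomized at even accrual, so less of the trial remains to be resized.
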